#### Recruitment {15}

##### Community sensitization

We first sought approval from the Homa Bay County Government Ministry of Health and based on their advice, hosted meetings with CHVs, village chiefs, and public health officers on Mfangano Island, and other key stakeholders from the county to explain the purpose, scope, objectives, methods, timeline, and potential significance of our study. CHVs and village leaders were asked to disseminate study information to and answer questions from community members. Feedback from CHVs and village leaders was sought, and regular meetings were held among CHVs, village leaders, and the study team to devise and refine approaches to engage communities. Finally, broad-level community consent to participate in the ceiling net trial was sought through CHVs and village chiefs.

##### Community census

After community sensitization and affirmation of agreement to participate provided by village chiefs, a census will be conducted by CHVs and experienced local research assistants to enumerate and record demographic information from all households in the health units that are receptive to our study. The following information will be collected from each household: (1) the number of residents; (2) the age, gender, and occupation of each resident; (3) the name of the school attended by each child; (4) the number, type, size, and functions of house structures; (5) the current LLIN ownership and usage; and (6) the GPS coordinates of the household. Written informed consent to participate in the ceiling net trial will be sought from the head of each household during census house visits.

### Assignment of interventions: allocation

#### Sequence generation {16a}

Random numbers are generated using Microsoft Excel 2016.

#### Concealment mechanism {16b}

Each cluster is assigned a computer-generated random number. The random numbers are then arranged in ascending order. Clusters with random numbers in the smaller half are assigned to the intervention arm, while those in the larger half are in the control arm.

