### Trial design {8}

The study is a cluster-randomized controlled trial with 10 clusters per arm (intervention and control), consisting of two cross-sectional school surveys after 6 months and 12 months of intervention and one cohort followed for 12 months in both arms. Each cluster is a health unit comprising approximately 100 households, including 500 individuals. Each health unit has an assigned community health volunteer (CHV) responsible for national health surveys and routine community health activities. This study also utilizes CHVs as messengers of study-related information and enumerators of the questionnaire surveys.

To evaluate the primary outcome, 150 schoolchildren will be recruited from each cluster. To evaluate the protective efficacy in reducing the cumulative incidence, 25 individuals will be recruited from each cluster and followed up for 12 months as a cohort. Residents of all age groups will be recruited to allow for the evaluation of the impact on asymptomatic and/or submicroscopic infections, which are also observed in adults. Cohort participants will be interviewed about their health conditions every 2 weeks by CHVs and are asked to provide a blood sample to monitor asymptomatic infection. The blood collection will be done by finger prick and venipuncture alternately. Five house structures in each cluster will be randomly selected and subjected to pyrethrum spray catches (PSC) for the entomological assessment. The mosquito sampling will be implemented 6 and 12 months after the intervention. Sampling will take place at the same structures at both time points.

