#### Sample size {14}

Parasite prevalence by microscopy among schoolchildren on Mfangano Island is approximately 20%, based on our previous study [26]. To detect the expected effect of 60% parasite prevalence reduction (to a prevalence of 8%) relative to control, with a power of 0.8, two-sided type 1 error of 5%, an intraclass correlation coefficient (ICC) for clusters of 0.063 (estimated based on our previous school study by assuming each school as a cluster), and average cluster size 150 (number of schoolchildren), the required number of clusters is 10 (or 1500 children) per arm using Stata/MP16.1. Based on the 2019 national census, children 3 to 15 years old account for 40.3% of the total population in Homa Bay County. The study requires a total population (all ages) of 7444 people or 1880 households (mean of 3.96 persons per household on Mfangano). By assuming a 3% dropout per month, we plan to enroll 1315 households for the intervention arm.

For the longitudinal cohort, we estimate the infection incidence on Mfangano Island as approximately 2.0 per person-year based on the data on Kenya Health Information System (KHIS). To detect the expected effect of a 40% reduction (1.2 per person-year), with a power of 0.8, two-side type 1 error of 5%, and an average cluster size of 25 individuals, the required number of clusters is 7 (or 350 individuals) per arm based on Eq. 7.3 on reference [27]. Assuming 3% of cohort participants will drop out per month, we plan to enroll 490 individuals in the cohort.

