### Data collection and management

#### Plans for assessment and collection of outcomes {18a}

##### Cross-sectional school surveys

Malaria prevalence in children will be estimated using cross-sectional malariometric surveys in schools. These surveys will be conducted at baseline (before ceiling net installation), 6 months, and 12 months post-installation. In addition, class rosters will be cross-referenced with the community census to determine the allocation of each eligible student in the trial clusters.

Malaria status will be determined using three methods: RDT, microscopy, and PCR. First, a finger prick blood sample will be collected for on-site diagnosis by Paracheck-Pf® RDT (Orchid Biomedical Systems, India). Survey participants with positive test results will receive a treatment course of artemether-lumefantrine with dosing instructions as per the guidelines from the Ministry of Health in Kenya. Blood smears will be prepared on-site and transported to the main laboratory in Homa Bay, where thin smears are fixed with methanol. All smears are stained with 3% Giemsa solution for 30 min, then examined by experienced microscopists. Two blood samples (70 µl each) will be collected with a 75-mm EDTA-coated micro-hematocrit capillary tube (Marienfeld, Lauda-Königshofen, Germany) and spotted on Whatman ET31 Chr filter paper (Whatman International. Maidstone, UK). The blood spots will be allowed to dry at ambient temperature and stored in individual zipped plastic bags at − 20 °C. The dried blood spots (DBS) will be used for DNA extraction and determination of malaria status by PCR [28].

Hemoglobin (Hb) levels will be measured using the HemoCue Hb 801 Analyzer (HemoCue, Ängelholm, Sweden). Survey participants with severe anemia based on the WHO criteria [29] will be referred to local health facilities for further consultation.

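### Allocation of the 20 clusters is valid but unrestricted, although census data come first; restricting it, or now adjusting for baseline cluster prevalence, would be a cheap improvement

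*Protocol article*

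**What the plan says.** The design is a "cluster-randomized controlled trial with 10 clusters per arm (intervention and control"). Under Sequence generation {16a}, "Random numbers are generated using Microsoft Excel 2016". Under Concealment mechanism {16b}, the numbers are put in ascending order and "Clusters with random numbers in the smaller half are assigned to the intervention arm"; the rest are controls. The fixed 10:10 split is the only restriction described.

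Three kinds of information bear on what could have been balanced:

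- **Census.** The Community census section lists household size, each child's school, the number, type and size of house structures, "the current LLIN ownership and usage; and (6) the GPS coordinates of the household". Consent is sought at the census visits. Table 2 puts consent at week -8 and allocation at week 0, so these data come before allocation.
- **Baseline school survey.** The Cross-sectional school surveys section says: "These surveys will be conducted at baseline (before ceiling net installation), 6 months, and 12 months post-installation". That places the baseline survey before installation, not before allocation. Table 2 shows allocation, installation and the school survey all at week 0.
- **Analysis.** The Statistical methods section {20a} names age, gender, bed net use, house structure and SES as adjustment variables, in a list that is left open. It does not name baseline cluster prevalence. The second stage is a Wilcoxon rank-sum test on cluster summaries.

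The Sample size section {14} supplies the variance input: "an intraclass correlation coefficient (ICC) for clusters of 0.063".

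**The concern.** With ten clusters per arm, most of the uncertainty comes from differences between clusters rather than between children. An unrestricted draw can put noticeably more high-transmission units in one arm, and recruiting more children per cluster barely reduces that risk. The same draw serves every outcome: school prevalence, anemia, cohort incidence, salivary IgG and mosquito density. The trial is open-label, so a visible baseline gap would invite the objection that the arms differed before any net was hung. Data that could have limited the gap were already being collected for other purposes. What is at stake is precision and credibility, not validity.

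**Working it through.** **Inputs** (Sample size {14} and Trial design {8}): control prevalence 0.20, target 0.08 (a 12-point effect), ICC 0.063, 150 children per cluster, 10 clusters per arm, two-sided 5%, power 0.8. The 5-point threshold is an assumption of this review.

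**1. The plan's own figure.**
- Individually randomised size: [1.96·√(2·0.14·0.86) + 0.842·√(0.20·0.80 + 0.08·0.92)]² / 0.12² = 130.07 per arm.
- Design effect: 1 + 149·0.063 = 10.387.
- Clusters: 130.07·10.387/150 = 9.007, rounded up to 10, which matches the plan. Power with 10 clusters is about 0.84 on this formula.

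**2. Baseline gap under the unrestricted sort.**
- Between-cluster variance: 0.20·0.80·0.063 = 0.01008, an SD of 10.0 points.
- Sampling variance of a cluster mean: 0.16·0.937/150 = 0.00100. The between-cluster share is 0.01008/0.01108 = 91%.
- SD of the observed arm difference: √(2/10·0.01108) = 0.0471, or 4.7 points. This is 39% of the 12-point effect.
- P(observed gap > 5 points) = 2·[1 − Φ(0.05/0.0471)] = 28.8%. A beta-binomial simulation gives 28.7%.
- Without sampling error the SD is √(2/10·0.01008) = 4.49 points, and P(true gap > 5 points) = 26.5%.

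**3. Sensitivity to the ICC** (observed gap above 5 points):

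| ICC | Chance |
|---|---|
| 0.01 | 3% |
| 0.02 | 9% |
| 0.03 | 14% |
| 0.063 | 29% |
| 0.10 | 39% |

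**4. A feature shared by half the clusters**, such as one side of the island. The chance of a 7:3 or worse split is 2·(120² + 45² + 10² + 1²)/184,756 = 17.9%.

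**5. What restriction would do.**
- Two strata of 10 on observed baseline prevalence, 5:5 within each (simulated): the gap SD falls to 2.9 points and the chance of a gap above 5 points to about 9%.
- Balancing on census variables only, with an assumed correlation r with cluster prevalence, taking the SD as 4.7·√(1 − r²): 27% at r = 0.3, 22% at 0.5 and 14% at 0.7. The documents give no value for r.

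**6. Power for 20% v 8%** (simulation: beta-distributed cluster prevalences, Gaussian copula linking baseline to 12 months, binomial sampling of 150). The plain rank-sum test gives about 0.83, or about 0.82 with a continuity correction. Two strata with the van Elteren test give:

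| Assumed baseline-to-12-month correlation | Power |
|---|---|
| 0 | 0.80–0.81 |
| 0.3 | 0.83 |
| 0.5 | 0.86 |
| 0.7 | 0.90 |

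Type 1 error is 4–5% for both schemes.

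**The case against.** The strongest reply is that nothing here is an error. Simple randomisation of clusters is valid. The variation behind the 29% is the same between-cluster variation that the sample size allows for through the ICC, and the cluster-level rank test measures the arm difference against it. Power is at or above the planned 0.8 without restriction. That stands. A reader might infer that a chance imbalance would pass undetected as a net effect, or that the test is too liberal; the documents support neither.

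A reader might also infer that baseline prevalence was available when the clusters were allocated. It is documented only as preceding installation, and Table 2 puts allocation in the same week. Only the census is shown to come earlier, and the benefit of balancing on census variables depends on a correlation that is not given.

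Nor is it established that restriction would recover lost power. At a correlation of 0.3 there is no gain, and near zero there is a small loss, because the stratified test gives up some comparisons.

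Three further points hold in part. The ICC was estimated with schools as clusters and is applied to health units. Adjustment for bed net use, house structure and SES already covers some of what the census could have balanced, and the open list leaves room for more. Cluster prevalence is also not ready on the survey day: class rosters must first be matched to the census.

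What survives is narrower: ten clusters per arm, useful balancing data collected in advance, and neither the allocation rule nor the named adjustment variables use baseline transmission.

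**Conclusion.** A cheap improvement, not a flaw in validity. On the plan's inputs, an observed baseline gap of more than 5 points, about 40% of the target effect, has a chance of about 29% (about 27% for the true gap). The figure runs from 9% at ICC 0.02 to 39% at ICC 0.10. It rests on the school-based ICC, on 150 children per cluster and on a threshold that the documents do not set. Two prevalence strata would have brought it to about 9%. The effect on power ranges from a loss of 0.02 to 0.03 to a gain of about 0.07 across assumed correlations of 0 to 0.7, so better balance is the firmer argument and power the conditional one.

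**What to change.** **As a design rule**, either of two routes:

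- Stratify or constrain the allocation on census location or LLIN use. This needs no new data and no change of schedule.
- State that allocation follows the baseline school survey. Link RDT results to clusters through the rosters and census, rank the 20 clusters, form two strata of 10, and assign 5:5 within each. Replace the second-stage Wilcoxon test with its stratified (van Elteren) form.

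The cost is protocol wording, a matching test and, for the second route, a short wait for the roster-to-census linkage. No extra participants or nets are needed.

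**For this trial**, the Trial status section shows installation finished in January 2022 and cohort follow-up in December 2022, so the allocation cannot be changed. The part that can still be used is in the analysis. Before arm codes are joined to the outcome data, add baseline cluster prevalence to the first-stage model of the cluster-level comparison, and commit to reporting baseline prevalence and census characteristics by arm. The cost is one cluster-level covariate with 20 clusters. Its benefit depends on the same unknown baseline-to-12-month correlation.

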#### Implementation {16c}

The allocation sequence and assignment are generated by a volunteer who has no knowledge about the study. Local study assistants will perform participant enrollment.

### Assignment of interventions: blinding

#### Who will be blinded {17a}

Due to the visibility of the Olyset®Plus ceiling net, neither the trial participants nor the members of the study team who take part in field activities can be blinded. However, laboratory- and office-based personnel (e.g., microscopists, laboratory technicians, and data analysts) will be blinded to the identity and intervention status of the trial participants since all biological specimens will be identified by a unique numeric study identifier, and personal information will be removed before analyses.

#### Procedure for unblinding if needed {17b}

This is an open-label trial, and only the data measurers are blinded. Therefore, there is no circumstance that they need to be unblinded.

### Data collection and management

#### Plans for assessment and collection of outcomes {18a}

##### Cross-sectional school surveys

Malaria prevalence in children will be estimated using cross-sectional malariometric surveys in schools. These surveys will be conducted at baseline (before ceiling net installation), 6 months, and 12 months post-installation. In addition, class rosters will be cross-referenced with the community census to determine the allocation of each eligible student in the trial clusters.

Malaria status will be determined using three methods: RDT, microscopy, and PCR. First, a finger prick blood sample will be collected for on-site diagnosis by Paracheck-Pf® RDT (Orchid Biomedical Systems, India). Survey participants with positive test results will receive a treatment course of artemether-lumefantrine with dosing instructions as per the guidelines from the Ministry of Health in Kenya. Blood smears will be prepared on-site and transported to the main laboratory in Homa Bay, where thin smears are fixed with methanol. All smears are stained with 3% Giemsa solution for 30 min, then examined by experienced microscopists. Two blood samples (70 µl each) will be collected with a 75-mm EDTA-coated micro-hematocrit capillary tube (Marienfeld, Lauda-Königshofen, Germany) and spotted on Whatman ET31 Chr filter paper (Whatman International. Maidstone, UK). The blood spots will be allowed to dry at ambient temperature and stored in individual zipped plastic bags at − 20 °C. The dried blood spots (DBS) will be used for DNA extraction and determination of malaria status by PCR [28].

Hemoglobin (Hb) levels will be measured using the HemoCue Hb 801 Analyzer (HemoCue, Ängelholm, Sweden). Survey participants with severe anemia based on the WHO criteria [29] will be referred to local health facilities for further consultation.

##### Cohort survey

Malaria incidence, exposure to *Anopheles* bites, will be assessed during and after 12 months of Olyset®Plus ceiling net installation. Every 2 weeks, CHVs will visit the homes of cohort participants. A structured questionnaire created using the Research Electronic Data Capture (REDCap) application and loaded on an Android-based tablet computer will be used to collect any history of fever, malaria episode, visit to the local health facilities, and travel in the previous 2 weeks [30].

Every month, certified medical laboratory staff will accompany CHVs on home visits to collect blood samples from cohort participants. Blood sampling by finger prick and venipuncture will alternate between monthly visits, starting with a finger prick at baseline. Blood samples will be used to determine malaria infection status by RDT, microscopy, PCR, and Hb measurement as described for the cross-sectional surveys. In addition, whole blood (500 µl for capillary blood and 3 ml for venous blood) will be collected in EDTA tubes. These samples will be transported to the main laboratory in Homa Bay County Teaching and Referral Hospital and stored at − 80 °C.

Training sessions will be held for CHVs to familiarize themselves with the questionnaire’s content and the REDCap application’s use to record the responses. Built-in validation and completion checks will ensure data quality and completeness, respectively. To avoid duplication, all microscope slides, filter papers, and sample tubes will be pre-labeled with auto-generated serial numbers. CHVs and certified medical laboratory staff will be prompted by the REDCap application before blood sampling to confirm the identity and serial number of the cohort participant. The completeness of blood sampling will be confirmed twice after the sampling step in the field and at the sample storage step in the laboratory.

##### Mosquito density, species composition, and infection rates

A cross-sectional entomological survey will be conducted to obtain baseline data before the intervention. Indoor-resting female anopheline mosquitoes will be sampled from five houses in each cluster using pyrethroid spray catches and light traps. All selected houses are made of mud walls and consist of one room. Using the baseline data, the cluster size (the number of houses) will be estimated for a post-intervention survey with a 50% density reduction and power of 0.8. The post-intervention survey will be conducted at the end of the rainy season during the study period. Sampled anophelines will be identified at the species level with PCR. The occurrence of *Plasmodium* parasites in the salivary glands of individual mosquitoes will also be examined using PCR.

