## Statistical methods

### Statistical methods for primary and secondary outcomes {20a}

The intention-to-treat (ITT) analysis is the primary analysis approach for both the primary and secondary outcomes, and the per-protocol analysis will be included as a supplementary analysis.

The primary outcome of the study is malaria prevalence by microscopy in schoolchildren (3 to 15 years old) 12 months after Olyset®Plus ceiling net installation. The results of microscopic examination from the cross-sectional survey 12 months after the implementation will be compared between the intervention arm and the control arm, based on cluster-level summaries using the two-stage procedure [27]. In the first stage, an individual-level logistic regression model will be constructed with adjustments for confounders, including age, gender, bed net use, house structure, and SES, and a fitting value will be summarized for each cluster using the model. In the second stage, a residual from the fitted values and the observed values for each cluster will be computed. The difference between the two groups will be tested using Wilcoxon’s rank-sum test by ranking cluster-level summaries.

As a secondary outcome, the malaria prevalence by PCR and anemia prevalence at 6 and 12 months after the implementation will be evaluated similarly. The cumulative malaria incidence during the 12-month follow-up will be analyzed based on the cohort follow-up data. Both symptomatic disease incidence and infection incidence, including asymptomatic infection, will be compared between the intervention and control arm based on cluster-level summaries. Entomological parameters, namely anopheline mosquito density, species composition, infection rate, and antibodies (IgG) against Anopheles salivary proteins gSG6 and cE5 at 6 and 12 months post-installation, will be analyzed in the same manner. Community members’ perceptions are analyzed qualitatively based on the questionnaire, focus group discussion, and in-depth interviews.

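### Baseline anopheline density is collected in every cluster but has no stated role in the density comparison, which can cost this secondary outcome some precision

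*Protocol article*

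**What the plan says.** All references are to the protocol article.

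- *Mosquito density, species composition, and infection rates*: "A cross-sectional entomological survey will be conducted to obtain baseline data before the intervention". Coverage is every cluster: "Indoor-resting female anopheline mosquitoes will be sampled from five houses in each cluster using pyrethroid spray catches and light traps". The selected houses are all one-room houses with mud walls. The only stated use of the result is sizing: "Using the baseline data, the cluster size (the number of houses) will be estimated for a post-intervention survey with a 50% density reduction and power" (target 0.8).
- *Outcomes {12}* lists anopheline density, species composition and sporozoite infection as a secondary outcome at 6 and 12 months after installation.
- *Statistical methods for primary and secondary outcomes {20a}* sets out a two-stage analysis of cluster-level summaries ending in a rank-sum test. The named adjustment variables are age, gender, SES, use of bed nets and house structure. The entomological parameters "at 6 and 12 months post-installation, will be analyzed in the same manner".
- *Trial design {8}* describes a "cluster-randomized controlled trial with 10 clusters per arm (intervention and control"), and also says: "Five house structures in each cluster will be randomly selected and subjected to pyrethrum spray catches (PSC) for the entomological assessment". It repeats the catches at 6 and 12 months in the same structures.
- *Concealment mechanism {16b}*: "Clusters with random numbers in the smaller half are assigned to the intervention arm". No stratification, matching or restriction is described.

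**The concern.** The effect on vectors is the third secondary objective and the trial's direct evidence that the nets act on mosquitoes. It rests on 20 clusters. Clusters may differ lastingly in mosquito density, and an unrestricted split can place the denser ones mainly in one arm.

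The named covariates can do little about this. Age and gender describe people, not a house catch. House structure has little room to vary, because all sampled houses are of one type. The measured variable closest to the outcome is each cluster's density before installation, and it has a stated role in sizing but none in the comparison. At stake is precision, together with a chance imbalance that no term in the stated analysis would absorb.

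**Working it through.** **The plan's own figure.** No sample size is stated for the entomological survey: there is no mean density, between-cluster variation or resulting number of houses. The 10 clusters per arm come from the primary outcome and do reproduce. For 20% v 8%, two-sided 5%, power 0.80, 131 children per arm are needed. The design effect is 1 + 149 × 0.063 = 10.387, and 131 × 10.387 / 150 = 9.07. Power is 0.7997 at 9 clusters and 0.840 at 10, so 10 per arm.

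**Textbook gain from baseline adjustment.** A t comparison of 10 v 10 cluster summaries (18 df) with power 0.80 has non-centrality 2.963. Adjusting for a baseline that correlates rho with follow-up cluster values divides the residual SD by √(1 − rho²), on 17 df:

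| observed rho (assumed) | power |
|---|---|
| 0 | 0.797 |
| 0.3 | 0.833 |
| 0.4 | 0.861 |
| 0.5 | 0.897 |
| 0.6 | 0.937 |

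If the baseline is useless, the cost is about 0.3 points.

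**What five houses do to the observed correlation.** For counts with mean m and dispersion 1, the error variance of a five-house log mean is about (1/m + 1)/5. The between-cluster log variance is ln(1 + CV²). Reliability is the second divided by the sum of the two. At m = 3 the error variance is (1/3 + 1)/5 = 0.267.

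- CV 0.4: ln(1.16) = 0.148; reliability 0.148/0.415 = 0.36.
- CV 1.0: ln(2) = 0.693; reliability 0.693/0.960 = 0.72.

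With five houses at both times, observed rho is at most about reliability × true correlation. A true correlation of 0.9 therefore gives about 0.32 at CV 0.4 and 0.65 at CV 1.0.

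**Simulation at the stated design.** Ten clusters per arm, five houses at both times, a true 50% reduction, negative binomial house counts with dispersion 1. Assumed: mean 1 or 3 per house, CV 0.4 to 1.0, true baseline-to-follow-up correlation 0.3 to 0.9. Selected results, 1,500 trials each:

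| mean | CV | true corr. | rank-sum, post only | log-scale regression on baseline | rank-sum on baseline residuals |
|---|---|---|---|---|---|
| 3 | 0.4 | 0.3 | 0.528 | 0.521 | 0.485 |
| 3 | 0.4 | 0.9 | 0.541 | 0.570 | 0.537 |
| 3 | 0.8 | 0.5 | 0.323 | 0.351 | 0.319 |
| 3 | 0.8 | 0.9 | 0.329 | 0.421 | 0.392 |
| 3 | 1.0 | 0.9 | 0.271 | 0.392 | 0.361 |
| 1 | 0.4 | 0.7 | 0.395 | 0.383 | 0.358 |
| 1 | 1.0 | 0.9 | 0.223 | 0.261 | 0.236 |

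Each power figure has a simulation error of about one point: √(0.27 × 0.73/1500) = 0.011. The largest difference here, 0.392 − 0.271 = 0.12, came out at about 0.11 on repeat. The regression therefore gains roughly 0 to 11 points. The rank-sum test on baseline-adjusted residuals changes power by about −3 to +8 points.

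**Chance imbalance.** The arm difference in mean true log density has standard error √ln(1 + CV²) × √(2/10), which is 0.172, 0.248, 0.315 and 0.372 for CV 0.4, 0.6, 0.8 and 1.0. The probability of an imbalance of at least 1.5-fold is 2 × [1 − Φ(ln 1.5 / SE)] = 2%, 10%, 20% and 28%.

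**The case against.** The strongest reply is that this argues from silence. The covariate list is introduced as a partial one, a separate analysis plan may exist, and the entomology section never says that sizing is the only use of the baseline. Age and gender cannot apply to a catch, so the entomological covariates must be settled somewhere else in any case. That stands to this extent: the protocol does not exclude baseline adjustment, and a reader who infers that it does goes beyond the text. It does not remove the point, because the article fixes a method, extends it to mosquito density, and gives a variable it already collects only a sizing role.

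Nor are the density comparisons wholly unadjusted. House structure, bed net use and SES could still enter, and restricting the catches to one house type limits variation by design.

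Two stronger readings are tempting, and the documents support neither:

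- *The comparison is biased.* It is not. Clusters are randomised and the test is at cluster level, so what is lost is precision and protection against chance imbalance.
- *Adjustment would lift power from 0.80 to about 0.90.* The arithmetic is right for an observed correlation of 0.5, but no document gives that correlation. Five baseline houses make it hard to reach unless clusters differ strongly. The starting value of 0.80 belongs to a later survey whose number of houses is still to be set, and to a t-test rather than the planned rank-sum test. If that survey is sized as intended, the target power is met without adjustment.

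Log-scale regression also has a weakness: the constant added for zero catches can matter when catches are sparse.

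**Conclusion.** The point holds as an inexpensive improvement to a secondary outcome, not as an error that threatens the trial. Baseline density is measured in all 20 clusters, its only stated use is sizing, and the stated density analysis does not name it.

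The expected gain is roughly 0 to 11 power points for a 50% reduction. It is near zero when clusters differ little, small when catches are sparse (at most about 4 points at a mean of one mosquito per house in the runs above), and near the top of the range only when clusters differ strongly and the differences persist. The chance of a true imbalance of at least 1.5-fold runs from 2% to 28% over the same assumed CVs. All means, CVs, correlations and the dispersion are assumptions, and the simulated figures apply to five houses per cluster at both times; a larger later survey would change them. No 10-point gain should be promised. Priority is minor to moderate.

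**What to change.** In *Statistical methods {20a}*, add a sentence stating that the anopheline density comparison at 6 and 12 months adjusts for each cluster's baseline density. The preferred form is a cluster-level regression of log mean catch on arm and log baseline mean catch, with the constant for zero catches fixed in advance. Entering baseline density in the first stage of the two-stage procedure and keeping the rank-sum test is possible, but it gains less and can gain nothing when clusters differ little.

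The same collection method must be used at both times. This needs a reconciliation first: *Trial design {8}* lists spray catches only, while the entomology section adds light traps. The number of post-installation houses should be settled in the same edit, because the former section fixes five and the latter leaves it to be estimated.

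The cost is one sentence and one degree of freedom (18 to 17). No new data are needed, because the baseline catches are already part of the plan.
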